#### Secondary outcome measurements

Secondary outcomes will be blood pressure, glucose parameter (fasting glucose, HbA1c, insulin, gamma-glutamyl transferase [GGT]), lipid profile (total cholesterol, triglycerides, high-density lipoprotein-cholesterol [HDL-C], low-density lipoprotein-cholesterol [LDL-C], free fatty acid, apolipoprotein A1 [Apo A1], apolipoprotein B [Apo B], high-sensitivity C-reactive protein [hs-CRP]), adipocytokine (leptin, adiponectin, ghrelin), and carnitine assay. These biomarkers will be checked at weeks 0 (baseline) and 12 (end of the trial). 24-hour dietary recalls were collected at the baseline and at the end of the trial. The schedule of assessments is presented in Table 1.

**Table 1 T1:** A brief study schedule at every visit

	** *Crossover design* **				
	** *Screening* **	** *Baseline* **			** *Follow up* **
	** *Visit 1* **	** *Visit 2, 5* **	** *Visit 3, 6* **	** *Visit 4, 7* **	** *(Visit 8)* **
	** *D-28* **	** *Week 0* **	** *Week 6* **	** *Week 12* **	** *Week 24* **
	** *~D-1* **	** *D0* **	** *D42* **	** *D84* **	** *D168* **
** *Informed consent form* **	◯				
** *Demographic information taking* **^ ** *1* ** ^	◯				
** *Medical history taking* **	◯				
** *Inclusion/exclusion criteria check* **	◯	◯			
** *Physician examination* **^ ** *2* ** ^		◯		◯	◯
** *Drinking/smoking taking status* **^ ** *3* ** ^		◯		◯	
** *Vital sign measurement* **	◯	◯	◯	◯	◯
** *Concomitant drugs check* **	◯	◯	◯	◯	◯
** *Anthropometric measures* **^ ** *4* ** ^		◯	◯	◯	◯
** *Glucose parameter* **^ ** *5* ** ^		◯		◯	
** *Lipid profile* **^ ** *6* ** ^		◯		◯	
** *Adipocytokine* **^ ** *7* ** ^		◯		◯	
** *Carnitine assay* **		◯		◯	
** *Laboratory test* **^ ** *8* ** ^		◯		◯	
** *Study product distribution* **		◯	◯		
** *Compliance checking* **			◯	◯	
** *Adverse event monitoring* **		◯	◯	◯	◯
** *Diet, physical exercisecounseling* **^ ** *9* ** ^		◯	◯	◯	◯

◯: Item need to be performed during the visit.

^1^ Sex, date of birth, age, contact address and phone number.

^2^ Include present illness, past history taking.

^3,9^Risk factors such as alcohol drinking, smoking, severe exercise and other dietary supplement intake will be managed.

^4^ weight, body mass index, body fat mass, percentage body fat, lean body mass, waist circumference, hip circumference, and waist to hip ratio.

^5^ fasting glucose, HbA1c, insulin, gamma-glutamyl transferase (GGT).

^6^ total cholesterol, triglycerides, high-density lipoprotein-cholesterol (HDL-C), low-density lipoprotein-cholesterol (LDL-C), free fatty acid, apolipoprotein A1 (Apo A1), apolipoprotein B (Apo B), high-sensitivity C-reactive protein (hs-CRP).

^7^ leptin, adiponectin, ghrelin.

^8^ Blood test (white blood cell [WBC], red blood cell [RBC], hemoglobin, hematocrit, platelets count, total bilirubin [TB], alkaline phosphatase [ALP], alanine transaminase [ALT], aspartate aminotransferase [AST], total protein, albumin, blood urea nitrogen [BUN], creatinine, creatine kinase [CK]), urine test (specific gravity, pH, nitrite, protein, glucose, ketone, urobilinogen, bilirubin, microscopic RBC/WBC).

### Statistical analysis and sample size

#### Baseline data and outcomes data

Statistical analysis will be performed using SAS version 9.3 for Windows (SAS Institute, Cary, NC, USA). Data will be presented as mean values and standard deviation (SD). The Chi-square test will be performed to determine differences at baseline in frequencies of categorized variables between the groups. A linear mixed-effects model will be applied to repeated-measures data for each continuous outcome variable. Fixed effects will be included treatment group, treatment visit, and interaction between treatment group and visit. When the analysis of variance indicated significant differences among groups, post hoc test (Turkey’s test) will be used to separate the differences between groups before and after the 12-week intervention period. A value of p < 0.05 will be considered statistically significant.

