#### Sample size

Sample size calculation is performed; primary outcome measure will be the percentage body fat, whereby 1.1% is assumed a clinically relevant difference between the two groups, with a standard deviation of 2.78%, alpha set on 5% and power on 80%. This resulted in a required number of 50 subjects in each group. Assuming a dropout rate of 20%, a total of 120 subjects will be enrolled in this trial.

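### Percentage body fat is measured at the start of each crossover period, but the listed model uses that baseline only as a response and names no primary contrast, so precision is lost by an amount the article does not allow one to fix

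*Protocol article*

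**What the plan says.** The trial is a two-period crossover with a 12-week washout (Design and setting). In Table 1 the row "Anthropometric measures" is ticked at week 0 (Visits 2 and 5, the start of each period), week 6 (Visits 3 and 6) and week 12 (Visits 4 and 7). Footnote 4 to that table includes percentage body fat. For the secondary biomarkers the article says: "These biomarkers will be checked at weeks 0 (baseline) and 12 (end of the trial)".

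Under Baseline data and outcomes data, a linear mixed-effects model is applied to the repeated measures of each continuous outcome: "Fixed effects will be included treatment group, treatment visit, and interaction between treatment group and visit". No baseline covariate appears, and the groups are not constrained to share a week-0 mean. The post hoc comparisons are described as covering group differences on both sides of the treatment period, which indicates that week 0 is a level of visit. The section does not say which term or contrast is the primary test.

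The Sample size section says "primary outcome measure will be the percentage body fat". It sizes the trial to detect a difference of 1.1 at 80% power and a 5% significance level, using an SD of 2.78, and arrives at 50 per group. It does not say what that SD describes.

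**The concern.** In a crossover each subject is already his or her own control. Subtracting each period's baseline as well can add more noise than it removes, and ignoring the baseline discards information when period-level differences persist from week 0 to week 12. Regression on the baseline gives it the weight the data support. The listed terms offer the first two options but not the third.

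At stake is precision on percentage body fat, and by the same algebra on each secondary outcome measured at weeks 0 and 12. Confidence intervals may be wider, and a true 1.1-point difference more easily missed, than the collected data require. The size of this for the secondary outcomes cannot be given, because the article has no variance figures for them.

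**Working it through.** **Inputs.** From the Sample size section: difference 1.1, SD 2.78, alpha 5% (taken as two-sided), power 80%, 50 per group, 20% dropout, 120 enrolled. Completers: 120 × 0.80 = 96. Not in the article: g, and the meaning of 2.78.

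**The plan's own figure.** Treating 2.78 as a within-subject SD in a two-period crossover, total N = 2 × 2.78² × (1.960 + 0.842)² / 1.1² = 100.3, or about 50 per sequence group. The stated 50 is reproduced.

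**What the interaction estimates.** The group-by-visit means are saturated. With complete data, the week-12 interaction coefficient is therefore the mean change on chungkookjang minus the mean change on placebo. A generalised least squares fit to a test data set agreed with the hand calculation (−0.3068 both ways).

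**Variances.** Let D0 and D12 be a subject's chungkookjang-minus-placebo differences at weeks 0 and 12, with equal variances and correlation g ≥ 0. Relative to the variance of D12:

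- difference of changes, D12 − D0: 2(1−g)
- direct week-12 contrast, D12: 1
- D12 adjusted for D0: 1 − g²

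The ratios to the adjusted contrast are 2(1−g)/(1−g²) = 2/(1+g) for changes and 1/(1−g²) for the direct contrast.

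| g | changes / adjusted | direct week 12 / adjusted |
|---|---|---|
| 0 | 2.00 | 1.00 |
| 0.25 | 1.60 | 1.07 |
| 0.5 | 1.33 | 1.33 |
| 0.75 | 1.14 | 2.29 |
| 0.9 | 1.05 | 5.26 |

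Simulation with 100 subjects and 4,000 replicates gave 2.05, 1.31, 1.14 and 1.03 for the changes ratio at g = 0, 0.5, 0.75 and 0.9.

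**The group main effect is no way out.** With visits 0 and 12 only, it estimates half the effect with relative variance (1+g)/2. Rescaled to the full effect, that is 2(1+g), so its efficiency against the adjusted contrast is (1−g²)/(2(1+g)) = (1−g)/2, never above one half.

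**Power on one reading.** Suppose 2.78 is the SD of one period's change and changes are independent across periods. The SD of the difference in changes is 2.78 × √2 = 3.93. With 96 completers the standard error is 3.93/√96 = 0.401, and the noncentral t gives 77% power. With 100 completers it is 80% by the normal approximation (79% by noncentral t). Adjustment multiplies the SD by √((1+g)/2). The direct contrast has SD 3.93/√(2(1−g)).

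| g | adjusted: SD, power (N = 96) | direct week 12: SD, power (N = 96) |
|---|---|---|
| 0 | 2.78, 97% | 2.78, 97% |
| 0.25 | 3.11, 93% | 3.21, 91% |
| 0.5 | 3.40, 88% | 3.93, 77% |
| 0.75 | 3.68, 83% | 5.56, 48% |

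If 2.78 is instead the SD of the difference in changes, power is already 97% as listed. Adjustment then adds under 5 points, though the interval narrows by 1 − √0.75 = 13% at g = 0.5 and 1 − √0.5 = 29% at g = 0.

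**The case against.** **The contrast is not fixed.** The section never names the interaction as the test, and its post hoc wording can be read as a direct comparison at week 12. At g = 0 that comparison loses nothing. This stands. A reader might infer that the plan has twice the variance it needs, but the documents do not support that: two is the ceiling, for one contrast at one value of g. What remains is that neither candidate contrast is efficient over the whole range of g.

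**The power figures are for a one-degree-of-freedom contrast.** For body fat, measured at weeks 0, 6 and 12, the interaction test has two degrees of freedom and is followed by post hoc comparisons. This stands. The 77% is the power of the week-12 change contrast, not of a test the article specifies.

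**Body fat is strongly correlated over time, so the loss must be small.** That is a parallel-group argument. The crossover comparison has already removed the stable between-subject part. One simulated case had g = 0 with an ordinary baseline to week-12 correlation of 0.94. A random subject intercept with independent errors also implies g = 0, but the article states no covariance structure, so g = 0 is an assumption too.

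**Planned power is roughly met.** If 2.78 is the SD of one period's change, the change contrast has close to the intended 80%. Adjustment is then additional precision, not repair of a failed calculation. This stands.

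**Change from period baseline protects against incomplete washout.** Suppose a residual chungkookjang effect c is present at week 0 of period 2 and persists unchanged to week 12. Averaged over the two sequences, D0 and D12 each shift by −c/2. The change contrast cancels this, adjustment with slope g leaves −(1−g)c/2, and the direct contrast leaves −c/2. This stands and is a real trade-off.

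**This belongs in the analysis plan.** An unseen plan may add a covariate, and the article does not call its list exhaustive. But the point is not silence: the fixed effects are stated, and as stated they are the less precise choice.

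**Conclusion.** The point holds as a loss of precision of uncertain size. The baseline is collected in each period and the listed terms use it only as a response. With g ≥ 0 and equal variances, no contrast obtainable from those terms at weeks 0 and 12 is more precise than the baseline-adjusted one, apart from a degree of freedom or two. The excess variance is 5% to 100% for the change contrast as g falls from 0.9 to 0. For the direct week-12 contrast it is nil at g = 0 and 33% at g = 0.5, and it rises steeply beyond. Whether power moves by 5 to 20 points or hardly at all depends on what 2.78 measures, which the article does not say.

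It would be wrong to conclude that the estimate is biased, that the type I error is affected, or that the trial is underpowered for this reason. None of these follows from the documents. Nor is this the same matter as the absence of period and sequence terms; adding those would not recover the lost precision.

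**What to change.** In Baseline data and outcomes data:

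- Name the week-12 chungkookjang-minus-placebo difference in percentage body fat as the primary contrast.
- Model the post-baseline values (weeks 6 and 12) as responses.
- Include the period-specific week-0 value as a covariate, split into the subject's mean over the two periods and the deviation from that mean. Regressing the within-subject week-12 difference on the week-0 difference is a simple alternative.
- Apply the same rule to each secondary outcome measured at weeks 0 and 12, using its own baseline.
- Keep the change-from-period-baseline analysis as a sensitivity analysis, because the covariate removes a persisting residual effect only in part.
- In the Sample size section, say which standard deviation 2.78 is.

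The cost is a change of wording, a few lines of code and one or two degrees of freedom. No further subjects, visits or measurements are needed. The statistical downside is the weaker protection if washout is incomplete, which the sensitivity analysis is there to show.

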### Design and setting

This is a 12 weeks, randomized, double-blinded, placebo-controlled crossover study. From February 2013 to December 2013, Obesity Research Center of Chonbuk National University and Chonbuk National University Hospital Clinical Trial Center in Korea will participate in this study. Recruitment will therefore be expected to be completed within the study period. To recruit the participants, we will advertise in the bulletin board and on the internet homepage of Chonbuk National University. Eligible participants will be randomly allocated into 2 group (the CKJ or placebo group) with 1:1 allocation ratio and receive treatment for 12 weeks. After a 12-week washout period, the groups will be crossed over. The evaluation of participants and the analysis of the results will be performed by professional blinded to the group allocation. Written consent will be obtained from each participant before the start of this study. Our study plan is summarized in Figure 1.

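### The stated mixed model (group, visit, group × visit) is a parallel-group model: it names no period or sequence term for a two-period crossover and defines no contrast that uses both periods.

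*Protocol article*

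**What the plan says.** Under Design and setting, the Protocol article describes the trial so: "This is a 12 weeks, randomized, double-blinded, placebo-controlled crossover study". It continues: "After a 12-week washout period, the groups will be crossed over". Table 1 shows the same structure. Visits 2 and 5 share the Week 0 column, Visits 3 and 6 the Week 6 column, and Visits 4 and 7 the Week 12 column. Anthropometry is taken at all six of these visits; the blood outcomes are taken at Weeks 0 and 12 of each period only.

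Under Baseline data and outcomes data the analysis is: "A linear mixed-effects model will be applied to repeated-measures data for each continuous outcome variable". The terms follow: "Fixed effects will be included treatment group, treatment visit, and interaction between treatment group and visit". If the analysis of variance is significant, a Tukey-type post hoc test "will be used to separate the differences between groups before and after the 12-week intervention period". That wording refers to one 12-week period. Period, sequence and the handling of second-period data are not mentioned.

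**The concern.** Group, visit and their interaction are the usual terms for two parallel groups followed over time. In a crossover each subject supplies both products, and the treatment effect is a within-subject difference between two periods. The model therefore has to say that treatment is the product taken, and has to keep differences between periods apart from differences between products.

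A period difference in the 12-week change is plausible here. The two baselines lie 24 weeks apart (12 weeks of treatment plus 12 of washout) within a study running "From February 2013 to December 2013", and diet and exercise counselling recurs at every visit from Visit 2 on. Unequal completion by sequence is possible too: 20% dropout is expected, and subjects with compliance of 70% or less count as dropouts.

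At stake are the definition of the primary treatment effect, its precision and, if dropout differs by sequence, its freedom from bias. This is a model that the article states, so the point is not a detail merely left to an unseen analysis plan.

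**Working it through.** **1. The plan's own figure.** The Sample size section gives a difference of 1.1 ("whereby 1.1% is assumed a clinically relevant difference between the two groups"), an SD of 2.78, alpha 5% and power 80%, hence 50 per group, 100 in all. The kind of SD and the sidedness are not stated; I assume a two-sided test, so (1.960 + 0.842)² = 7.849.

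- Crossover, 2.78 as within-subject SD: total N = 2 × 2.78² × 7.849 / 1.1² = 100.26. This reproduces the stated total of 100 to within rounding. The SD of differences is then √2 × 2.78 = 3.93.
- Crossover, 2.78 as SD of differences: total N = 2.78² × 7.849 / 1.1² = 50.13, which matches 50 only as a total.
- Parallel groups, 2.78 as SD of the compared quantity: 100.26, so 101 per group. With 50 per group the power is Φ(1.1 / (2.78 × √(2/50)) − 1.960) = Φ(0.018) = 51%.

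The stated size therefore fits a crossover analysis using both periods, not a comparison of two groups over one period.

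**2. What the stated terms can mean.**

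| Group | Visit | Result |
|---|---|---|
| Product taken | Week within period (Table 1 columns) | Treatment effect estimable; period difference in the change goes into the error |
| Randomised sequence | Week within period | Each group averages CKJ and placebo; with balanced data the contrast has expectation zero |
| Randomised sequence | Visits 2 to 7 coded separately | Period is carried by visit and the effect is recoverable from the interaction, but the stated between-group comparison is not that contrast |

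**3. Size on the first reading.** Take each subject's CKJ-minus-placebo difference in 12-week change, a simplification because the random effects are not stated. Let τ be the treatment effect and p the Period 2 minus Period 1 shift in the change. The expected difference is τ − p for CKJ-first subjects (n₁) and τ + p for placebo-first subjects (n₂).

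With equal sequences and no period term, variance = SD² + p²:

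| SD of differences | p = 1.0 | p = 2.0 |
|---|---|---|
| 2.78 (variance 7.73) | 8.73, ratio 1.13 | 11.73, ratio 1.52 |
| 3.93 (variance 15.46) | 16.46, ratio 1.06 | 19.46, ratio 1.26 |

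Bias of the estimate = p × (n₂ − n₁) / N. With 96 completers (80% of 120) split 52/44, its size is 8/96 = 0.083 per 1.0-point shift, or 7.6% of 1.1. Split 56/40, it is 16/96 = 0.167, or 15% of 1.1.

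**4. Simulation.** 20,000 trials per scenario, 100 completers split 50:50, true difference 1.1:

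| SD of differences | p | Power without / with period term | Type I error without / with |
|---|---|---|---|
| 2.78 | 1.1 | 96.5% / 97.6% | 3.6% / 5.2% |
| 2.78 | 2.2 | 92.1% / 97.5% | 1.3% / 4.9% |
| 3.93 | 1.1 | 77.0% / 79.3% | 4.1% / 4.8% |
| 3.93 | 2.2 | 70.1% / 79.0% | 2.3% / 5.1% |

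With completers split 56:44 and p = 2.2, the mean estimate without a period term is about 0.84 (1.10 − 2.2 × 12/100 = 0.836); with the term it stays at 1.10. With p = 0 the two analyses agree.

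**The case against.** The strongest reply is that this is a condensed article, that a separate analysis plan may exist, and that the list of effects is not said to be exhaustive. Covariates, random effects and carryover checks are indeed normal analysis-plan content, and their absence is not the point. But the article does choose a set of fixed effects, and that set does not match the design.

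Four stronger readings are tempting and are not supported.

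- *That visit cannot absorb a period difference.* Table 1 also numbers Visits 2 to 7 separately. Coded so, with group as sequence, the model carries period. What is still missing is the right contrast.
- *That the treatment effect is not estimated at all.* This needs group to mean sequence and visits to be pooled by week. The article speaks of a CKJ group and a placebo group, which favours the product reading, where the effect is estimable.
- *That carryover would go unseen.* On the product reading, the Week 0 contrast pools Visits 2 and 5. With complete, equal sequences it equals half the between-sequence difference in Visit 5 minus Visit 2. The planned before-and-after comparison covers it, though only after a significant overall test.
- *That different seasons at the two baselines by themselves distort the result.* Each period has its own baseline, so a level difference cancels from the contrast in change. Only a difference in the 12-week change matters.

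The sizes are also open to challenge. Shifts of 1.0 and 2.0 points are large beside a 1.1-point target. If dropout is unrelated to sequence, a split of 52/44 or worse among 96 completers has probability about 0.11, and 56/40 or worse about 0.0004 (hypergeometric, 24 dropouts among 60 + 60). The 56/40 case therefore needs dropout that depends on sequence. This limits the likely bias; it does not justify leaving period out.

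**Conclusion.** The point stands: the stated model is a parallel-group model applied to a crossover, and the primary treatment contrast is not uniquely defined. On the most natural reading, the consequence is loss of precision if the 12-week change differs between periods: 13% to 52% more variance for assumed shifts of 1.0 to 2.0 points if the SD of differences is 2.78, and 6% to 26% if it is 3.93. With equal completers per sequence the estimate is unbiased and the test conservative. With unequal completers there is bias as well, 0.083 per 1.0-point shift at 52/44.

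The period shifts, the completer splits and the meaning of 2.78 are assumptions; the article gives no period shift and does not say which SD it used. A reader might infer that the trial as planned cannot detect an effect of CKJ. That follows only from the less natural sequence-pooled reading and should not be claimed.

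**What to change.** Reword the analysis paragraph so that treatment is the product taken in each period, and fit a mixed model with fixed effects for sequence, period and product and a random subject effect.

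- **Anthropometric outcomes (Weeks 0, 6 and 12):** add week, product × week and period × week, with a random subject-within-period effect. The primary estimate is CKJ minus placebo at Week 12, adjusted for or as change from the period baseline, with a 95% confidence interval.
- **Outcomes measured only at Weeks 0 and 12:** analyse the Week 12 value of each period with sequence, period, product, the period-specific baseline and the subject's mean baseline. With one post-baseline value per period, week terms and a subject-within-period effect cannot be fitted.
- **Carryover:** report the between-sequence difference in Visit 5 minus Visit 2, and the Period 1-only estimate, as descriptive sensitivity checks. Neither should serve as a pre-test that decides the primary analysis.

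The cost is a rewritten paragraph and a few degrees of freedom. Table 1 already schedules every measurement needed.

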#### Primary objective

To evaluate the efficacy of the CKJ on anthropometric parameter in overweight/obese subjects after 12 weeks of consumption.

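### The 12-week comparison is a post hoc step behind an omnibus test that, with anthropometry also taken at Week 6, does not isolate the 12-week effect

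*Protocol article*

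**What the plan says.** The primary objective is "To evaluate the efficacy of the CKJ on anthropometric parameter in overweight/obese subjects after 12 weeks of consumption".

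Table 1 marks the row "Anthropometric measures" at Week 0, Week 6 and Week 12 of each period and again at the Week 24 follow-up (Visit 8). The row "Study product distribution" is marked only at Weeks 0 and 6, so Visit 8 is off treatment. The biomarkers among the secondary outcomes are taken only at Weeks 0 and 12.

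Under Baseline data and outcomes data, "A linear mixed-effects model will be applied to repeated-measures data for each continuous outcome variable". The terms are then listed: "Fixed effects will be included treatment group, treatment visit, and interaction between treatment group and visit". The next sentence adds a Tukey-type post hoc test, to be run when the analysis of variance is significant, which "will be used to separate the differences between groups before and after the 12-week intervention period".

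The Sample size section works from one difference in percentage body fat: "1.1% is assumed a clinically relevant difference between the two groups", with an SD of 2.78%, alpha of 5% and power of 80%.

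**The concern.** The model is worded once for all outcomes. For a biomarker seen only at Weeks 0 and 12, with visit coded within period, the group-by-visit term has 1 df and is the 12-week effect. For the primary outcome the Week 6 measurement breaks that match. The term that opens the way to the 12-week comparison becomes a joint test over several visits, or an average over them.

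Two things are at stake. First, power planned for one difference is partly spent on a broader question, so a real 12-week effect can be stopped at the gate before it is examined. Second, a significant omnibus result could be reported as if it answered the primary objective, although a difference at Week 6 alone could have produced it.

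**Working it through.** **Inputs.** From the Sample size section: difference 1.1, SD 2.78, alpha 5%, power 80%, 50 per group. Assumed: a two-sided test; categorical visit with Weeks 0, 6 and 12 in the model; a large-sample (chi-square) approximation; the post hoc step taken as an unadjusted 5% contrast. The correlation between visits and the share of the effect present at Week 6 are not in the document, so both are varied.

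**The plan's own figure.** Reading 2.78 as a within-subject SD in a two-period crossover, total N = 2 × (2.78 × (1.960 + 0.842) / 1.1)² ≈ 100.3, or 50 per sequence. This matches the stated 50 and is a calculation for a single difference (1 df). A parallel-group formula gives 101 per group and does not match. The results below do not depend on which reading of the SD is right.

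**Degrees of freedom.** With two groups, interaction df = number of visits − 1, so Weeks 0, 6 and 12 give 2.

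**Gate power.** A 1-df test with 80% power has noncentrality λ = (1.960 + 0.842)² = 7.85. At that same λ a 2-df test has 70.9% power. Restoring 80% at the gate needs λ = 9.63, a ratio of 9.63 / 7.85 = 1.23, or about 23% more information.

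**When the worst case applies.** With correlation r between the Week 6 and Week 12 changes (equal variances) and a fraction f of the effect present at Week 6, the 2-df noncentrality is λ(1 − 2rf + f²)/(1 − r²). It is smallest, and equal to λ, at f = r. If the measurements are equally correlated, r = 0.5, so an effect that builds steadily (f = 0.5) is exactly the worst case. A first-order autoregressive structure gives the same answer.

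**Both steps together.** I simulated the two change estimates with the contrast fixed at 80% power. The ranges run from equal correlation to autoregressive correlation of up to 0.9.

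| Share of effect at Week 6 | 2-df gate significant | Gate and Week 12 contrast both significant |
|---|---|---|
| 0.5 | 71% | 70% |
| 0.25 or 0.75 | 75–80% | 72–74% |
| 0 or 1 (abrupt) | 83–94% | 76–79% |
| Full 1.1 at Week 6, none at Week 12 | 83% to over 99% | about 5% |

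If the changes are correlated at 0.7 or 0.9 instead, the worst case moves to a larger Week 6 share but the floor stays at about 71% (gate) and 70% (both). For example, at r = 0.9 an effect fully present by Week 6 gives 73% and 71%, while a half effect gives 94% and 79%.

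**If the gate is the group main effect.** Averaging a profile of 0, 0.5 and 1 over Weeks 0, 6 and 12 gives (0 + 0.5 + 1) / 3 = 0.5, so the tested quantity is half the 12-week effect. I have not put a power figure on this, since it depends on variances the document does not give.

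**The case against.** The strongest reply is that the plan does aim at 12 weeks: the post hoc sentence compares the groups before and after the intervention period. This largely stands against one inference. A reader might conclude that a difference confined to Week 6 would produce a positive 12-week finding at least 83% of the time. That is the rate for the omnibus test alone. Once the post hoc step is applied, a Week 12 claim follows only about 5% of the time. The step does not remove the power cost, because it is reached only through the gate, and it is not worded as a product difference in 12-week change.

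A reader might also infer that Visit 8 enters the model, giving a 3-df test with about 64% power at the same noncentrality. The document does not support this. The model refers to treatment visits, and Table 1 labels Visit 8 as follow-up with no product given out. Nor does it fix how visit is coded or name the interaction as the gate. The 2-df figure is therefore conditional, but the other natural gate, the group main effect, misses Week 12 as well.

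Finally, visit coding and contrasts are often left to an analysis plan, and none is shown here. That would answer a mere silence. Here the article already states the model terms, the condition and the follow-up test, and that stated sequence does not match the objective.

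**Conclusion.** The point holds as a mismatch between the stated testing sequence and the primary objective, and it should be corrected. If visit is categorical and the interaction is the gate, the two-step procedure has about 70% power in the worst case, against 80% for a direct Week 12 contrast. It has about 72–74% when a quarter or three quarters of the effect is present at Week 6, and usually closer to 80% for abrupt effects. The gate itself can exceed 80% for abrupt effects, so a loss of power at the gate is a risk and not a certainty.

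These figures assume the contrast has exactly 80% power and that the post hoc step carries no further adjustment. A Tukey adjustment over more than one comparison would lower the two-step figures, by an amount not computed here. The problem concerns anthropometry; it does not arise for biomarkers taken only at Weeks 0 and 12 when visit is coded within period.

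**What to change.** In Baseline data and outcomes data, name the primary test as the single 1-df CKJ-minus-placebo contrast in percentage body fat at Week 12, as change from the period baseline, and state that it does not depend on any overall F test. Say that Week 6 stays in the model as supportive data and that the off-treatment Visit 8 is reported descriptively.

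The cost is one or two sentences and one contrast statement in SAS, with no new data. The small downside is that the primary test gives up the omnibus test's sensitivity to an abrupt effect or one seen only at Week 6.
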